## **Appendix 14: Fagerström Test of Nicotine Dependence (FTND)(Heatherton, Kozlowski, Frecker, & Fagerstrom, 1991)**

1. How soon after you wake up do you smoke your first cigarette?  
3= Within 5 minutes  
2= 6-30 minutes  
1=31-60 minutes  
0= More than 60 min
2. Do you find it difficult to refrain from smoking in places where it is forbidden, (e.g. in church, at the library, in the cinema)?  
0 = No  
1 = Yes
3. Which cigarette would hate most to give up?  
1 = The first one in the morning  
0 = All others
4. How many cigarettes per day do you smoke?  
0= 10 or less  
1= 11-20  
2= 21-30  
3= 31 or more
5. Do you smoke more frequently during the first hours after waking than the rest of the day?  
0 = No  
1 = Yes
6. Do you smoke when you are so ill that you are in bed most of the day?  
0 = No  
1 = Yes

Calculate: Add scores of all 6 items.

1-2 = low dependence  
3-4 = low-moderate dependence  
5-7 = moderate dependence  
8+ = high dependence

## Appendix 15: Mood and Physical Symptoms Scale-2 (MPSS-2)(West & Hajek, 2004)

*The next questions are about how you have been feeling over the past 24 hours.*

1. How much of the time have you felt the urge to smoke in the past 24 hours?

0=Not at all

1=A little of the time

2=A lot of the time

3=Almost all of the time

4= All of the time

2. How strong have the urges been?

0=No urge

1=Slight

2=Moderate

3=Strong

4=Very Strong

5=Extremely Strong

3. Calculate: Please add scores of questions above

0-2 = Mild

3-6 = Moderate

7-10 = Severe

**Appendix 16: Patient Health Questionnaire-2 (PHQ-2)(K. Kroenke, Spitzer, & Williams, 2003) and question 9 of Patient Health Questionnaire-9 (K. Kroenke et al., 2003; Kroenke, Spitzer, & Williams, 2001)**

Over the past two weeks, how often have you been bothered by any of the following problems?

|                                                                               | Not at all | Several days | More than half the days | Nearly every day |
|-------------------------------------------------------------------------------|------------|--------------|-------------------------|------------------|
| 1. Little interest or pleasure in doing things                                | 0          | 1            | 2                       | 3                |
| 2. Feeling down, depressed or hopeless                                        | 0          | 1            | 2                       | 3                |
| 9. Thoughts that you would be better off dead or hurting yourself in some way |            |              |                         |                  |

**Scoring**

If the sum of the answers to 1 and 2 are  $\geq 3$ , a mood disorder is indicated.

If the sum of the answers to 1 and 2 are  $< 3$ , a mood disorder is not indicated.

## Appendix 17: Generalized Anxiety Disorder 2-item Scale (GAD-2) (Plummer, Manea, Trepel, & McMillan, 2016)

### GAD-7

Over the last 2 weeks, how often have you been bothered by any of the following problems?

|                                               | Not at all | Several days | More than half the days | Nearly every day |
|-----------------------------------------------|------------|--------------|-------------------------|------------------|
| 1. Feeling nervous, anxious or on edge        | 0          | 1            | 2                       | 3                |
| 2. Not being able to stop or control worrying | 0          | 1            | 2                       | 3                |

3. Calculate: Add scores of GAD-7 Responses together for total  
0-2= Negative screen  
3-6= Positive screen

## Appendix 18: Perceived Stress Scale (PSS-4)(Cohen, Kamarck, & Mermelstein, 1983)

The next set of questions asks you about your feelings and thoughts during the last month. In each case, please indicate with a check how often you felt or thought a certain way.

1. In the last month, how often have you felt that you were unable to control the important things in your life?  
0=never  
1=almost never  
2=sometimes  
3=fairly often  
4=very often
2. In the last month, how often have you felt confident about your ability to handle your personal problems?  
0=never  
1=almost never  
2=sometimes  
3=fairly often  
4=very often
3. In the last month, how often have you felt that things were going your way?  
0=never  
1=almost never  
2=sometimes  
3=fairly often  
4=very often
4. In the last month, how often have you felt difficulties were piling up so high that you could not overcome them?  
0=never  
1=almost never  
2=sometimes  
3=fairly often  
4=very often

5. Calculate: Add scores of above responses

0-5 = Low Stress

6-11 = Moderate Stress

12-16 = High Stress

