#### Exploratory Objectives

6. To assess potential baseline (pre-intervention) predictors of abstinence including self-reported dependence, stress, anxiety, depression, alcohol and drug use, and self-efficacy. If a baseline variable is found to be associated with abstinence, it will be further assessed as a moderator of abstinence.
7. To assess change in self-reported measures at baseline (pre-quit) to 2- and 12-weeks post TQD on repeated standardized measures of nicotine dependence, stress, anxiety, depression, alcohol and drug use, and self-efficacy. If a measure is found to change significantly from baseline to a post quit time point, it will be assessed as possible mediator of abstinence outcomes.
8. To compare phone-assessed non-standardized single item questions on urges, withdrawal, motivation to quit smoking or remain abstinent, and confidence in ability to quit or remain abstinent at 1, 2, 6, 12, 26 and 52 weeks post-TQD. If a measure is found to change significantly from baseline to a post quit time point, it will be assessed as a possible mediator of abstinence outcomes. Phone assessments will be compared at specific time points and also across multiple time points using multi-level modeling.

9. To compare baseline scores on anxiety, depression, and stress for their effect on allocation to Responder or Non-Responder status in the adaptive and standard treatment arms.
10. To conduct cost-benefit analyses on allocation to adaptive vs standard treatment from the perspective of multiple stake holders: smokers, healthcare systems (clinics/hospitals), insurance companies, and employers.

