**Assessment of potential moderators of primary effect:** The following constructs will be assessed as potential predictors of abstinence: demographics (age, gender, race, education), smoking history and heaviness, financial status, dependence (measured by FTND), urge rating (measured by MPSS), depression (measured by PHQ-2), anxiety (measured by GAD-2), alcohol use (measured by AUDIT-C), stress (measured by PSS-4), and self-efficacy questions. Constructs that demonstrate an association with abstinence will be analyzed for potential moderation. Tests for differential associations of effects of baseline characteristics by randomization status on week-12 smoking abstinence will be based on interaction terms crossing randomization status (group) with the tested (putative) baseline predictor. Significance of the estimated coefficient associated with the interaction term would indicate that the effect of the tested predictor on abstinence varied differentially by treatment assignment. For each baseline predictor, we hypothesize that baseline will be equivalent across all randomized arms. In a second series of tests, the above protocol will be used to test for differential rates of change in abstinence associated with putative constructs (scales): urge (MPSS-2), stress (PSS-4), depression (PHQ-2), anxiety (GAD-2). As above, the primary test statistic will be based on interaction term crossing the tested scale with group.

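### Appendix 18 adds the four PSS-4 items without reversing the two positively worded ones, so the printed stress total cannot validly rank participants; only exploratory analyses are affected

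*Protocol*

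**What the plan says.** Appendix 18 of the Protocol prints the four PSS-4 items, each with the same response codes, 0 for never up to 4 for very often.

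- Item 1: "how often have you felt that you were unable to control the important things in your life"
- Item 2: "how often have you felt confident about your ability to handle your personal problems"
- Item 3: "how often have you felt that things were going your way"
- Item 4: "how often have you felt difficulties were piling up so high that you could not overcome them"

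The only scoring step is "5. Calculate: Add scores of above responses". Three bands follow: 0-5 low, 6-11 moderate, and "12-16 = High Stress".

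Section 10.7.5 names the PSS-4 as the standardized stress measure and points to this appendix. Section 13.5.1 lists "stress (measured by PSS-4") among the potential predictors and moderators of abstinence, and names the scale again for the second series of scale-by-group tests and as a candidate mediator. Section 3.1 uses stress in exploratory objectives 6, 7 and 9; objective 9 reads in part "To compare baseline scores on anxiety, depression, and stress for their effect on allocation to Responder or Non-Responder status".

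**The concern.** The bands treat a high total as high stress, but two of the four items run the other way. A participant who often feels confident and often finds that things go well adds up to 8 points to a total that is meant to measure stress. With equal weight on the two pairs, what items 1 and 4 add, items 2 and 3 take away.

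At stake is whatever the trial reports about stress: whether it predicts abstinence, modifies the treatment effect, changes with treatment, or relates to responder status. Several of these analyses run in stages. A baseline construct goes on to moderation testing only if it is associated with abstinence, and to mediation testing only if it changes or shows a positive finding. A mis-scored scale could be dropped at the first stage as unrelated, or go forward for a reason that has little to do with overall stress.

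**Working it through.** **Inputs.** The item wording, the 0-4 codes, the summing instruction and the three bands all come from Appendix 18. The item loadings in step 4 are assumptions; the Protocol gives none.

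**1. What the plan's own range implies.** Four items at 0-4 give totals of 0 to 16, so the printed range reproduces. For the labels to hold, the least stressed answers should fall in 0-5 and the most stressed in 12-16.

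**2. Consistent answer patterns.** Let items 1 and 4 equal k and items 2 and 3 equal 4-k, with k = 0 for no stress and k = 4 for maximal stress.

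- Printed total = k + (4-k) + (4-k) + k = 8 for every k.
- Total with items 2 and 3 reversed = k + [4-(4-k)] + [4-(4-k)] + k = 4k.

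| Answers (items 1 to 4) | Printed total and band | Reversed total and band |
|---|---|---|
| 0, 4, 4, 0 | 8, moderate | 0, low |
| 1, 3, 3, 1 | 8, moderate | 4, low |
| 2, 2, 2, 2 | 8, moderate | 8, moderate |
| 3, 1, 1, 3 | 8, moderate | 12, high |
| 4, 0, 0, 4 | 8, moderate | 16, high |

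A printed total of 16 needs very often on all four items, and a total of 0 needs never on all four. Both sets of answers contradict themselves, and both score 8 after reversal. The printed bands work only with the reversal that the key omits.

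**3. All possible patterns.** There are 5 × 5 × 5 × 5 = 625 answer patterns. Across them, with equal weight, the printed and reversed totals correlate 0.00. By band:

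| Band after reversal | Patterns | Printed low | Printed moderate | Printed high |
|---|---|---|---|---|
| High (12-16) | 70 | 9 | 56 | 5 |
| Low (0-5) | 122 | 23 | 90 | 9 |

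**4. Relation to true stress.** Assume one stress factor, with loading a on items 1 and 4 and b (in the opposite direction) on items 2 and 3. Before rounding to five categories:

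- r(printed) = 2(a-b) / √(4 + 2a² + 2b² - 8ab)
- r(reversed) = 2(a+b) / √(4 + 2a² + 2b² + 8ab)

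The first is zero when a = b and takes the sign of a-b otherwise. For a = 0.8 and b = 0.3, r(printed) = 1.0/√3.54 = 0.53 and r(reversed) = 2.2/√7.38 = 0.81. Simulation of 200,000 respondents with five-category items gives slightly lower figures:

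| a / b | Printed total | Reversed total |
|---|---|---|
| 0.5 / 0.5 | 0.00 | 0.74 |
| 0.6 / 0.6 | 0.00 | 0.81 |
| 0.7 / 0.7 | 0.00 | 0.87 |
| 0.8 / 0.6 | +0.25 | 0.88 |
| 0.6 / 0.8 | -0.25 | 0.88 |
| 0.8 / 0.5 | +0.35 | 0.85 |
| 0.5 / 0.8 | -0.35 | 0.85 |
| 0.8 / 0.3 | +0.50 | 0.79 |
| 0.3 / 0.8 | -0.50 | 0.79 |

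**5. Is the reversal given anywhere else?** No. Sections 10.7.5 and 13 name the scale but give no scoring rule. Where another scale needs a direction, the form builds it into the codes: item 1 of the FTND in Appendix 14 runs from 3 for the earliest cigarette to 0 for the latest. Appendix 18 does not do this.

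**The case against.** The strongest reply has four parts.

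*The analyst may not use the printed total.* Section 13 never refers to the summing line or the bands, similar calculation lines elsewhere are form-level steps, the appendix names a published instrument as its source, and analyses run under a designated statistician. The error could be put right silently. That is possible, but Appendix 18 is the only key that the Protocol states, and staff who follow it will compute and label the wrong total. The rule is printed and wrong, so it is not a detail left to a statistical analysis plan.

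*Nothing decisive depends on it.* This stands. The PSS-4 sets no eligibility rule, no randomization, no responder classification and no treatment. The primary and secondary outcomes and the sample size do not use it.

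*The zero correlation rests on equal loadings.* This also stands. A reader might infer that every stress analysis would be meaningless, or that any positive stress result would be spurious. The documents do not support that. They give no item loadings, and with unequal loadings the printed total carries some signal, of uncertain sign. The conclusion also holds only if the printed total is the one analysed.

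*Few real respondents are perfectly consistent.* Fair. A reader might infer that every highly stressed participant scores exactly 8. That is exact only for the consistent patterns; in simulation with equal loadings of 0.5 to 0.7, about 22-30% of the most stressed tenth do. The band counts matter only if the bands are reported or analysed, and the plan speaks of scores and scales.

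**Conclusion.** The scoring key is wrong as written. From the item wording and the bands alone, the printed PSS-4 total cannot validly rank participants by stress. The cancellation to 8 for consistent patterns and the band counts over the 625 patterns are exact. The size of the damage in real data depends on assumed loadings: over 0.3 to 0.8, the correlation with true stress runs from about -0.5 to +0.5 for the printed total and from about 0.74 to 0.88 after reversal. The fair description is that its sign and size are unreliable.

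The reach is limited to the exploratory predictor, moderator, mediator and responder-status analyses that use stress. This should be fixed before those analyses are run; it does not threaten the trial's main conclusion.

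**What to change.** Change the scoring line in Appendix 18 so that items 2 and 3 are scored as 4 minus the response before the four items are added. The range of 0-16 and the three bands can stay as printed, since they then work as labelled.

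State that the four item answers are kept as well as the total. Section 13.4 says that measures from study visits are captured in the EMR but does not say whether items or only totals are stored. If the items were stored, rescore all records already collected. If only totals were kept, the correct score cannot in general be recovered, because the same printed total arises from opposite answers. Use the corrected total in exploratory objectives 6, 7 and 9 and in the moderator and mediator analyses.

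The cost is one line in the appendix and a change to the scoring program, with no new data and no added burden on participants if item answers are available.

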#### **Exploratory Objectives**

6. The following baseline self-report assessment outcomes will predict biochemically confirmed 30-day continuous abstinence at 12 weeks post TQD and 7-day point prevalence abstinence at 2- and 12-weeks post-quit: nicotine dependence, depression, anxiety, stress, alcohol use, drug use, motivation, and self-efficacy.
7. The following baseline self-report assessment outcomes will predict lower number of cpd and higher number of days abstinent at 2- and 12- week visits: urge, withdrawal symptoms, depression, anxiety, stress, alcohol use, drug use, motivation, and self-efficacy.
8. The following baseline self-report assessment outcomes will predict abstinence on phone-based self-report at 1, 2, 6, 12, 26, and 52 weeks post-TQD urges, withdrawal, motivation to quit smoking or remain abstinent, and confidence in ability to quit or remain abstinent
9. Baseline scores on anxiety, depression, and stress will moderate the effect of allocation to Non-Responder status in the adaptive and standard treatment arms. This finding will show that poor response to pharmacotherapy may be related to high levels of anxiety, depression, or stress.
10. A prospective economic analysis of adaptive vs standard treatment will show cost-benefit outcomes from the perspective of people that smoke cigarettes, healthcare systems, insurance companies, and employers.
11. **Feasibility:** Demographics of patients at DSCP and Duke CSC will reflect the recruitment area
12. **Feasibility:** Medications used will show wide variation of use.
13. **Feasibility:** Attendance at DSCP Return Appointments will be favorable.
14. **Feasibility:** Referral Routes to DSCP will reflect recruitment area.
15. **Feasibility:** Medication side effects will be favorable.
16. **Feasibility:** Medication adherence will be favorable.

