**Economic Analysis:** An economic analysis of Adaptive vs. Non-Adaptive pharmacotherapy will be conducted. [name], PhD, MBA, a Duke University Health Economist with expertise in cost-benefit analysis for healthcare system program operation will conduct this analysis and oversee prospective data-collection on cost and time for all necessary TSCP operations to generate a prospective economic analysis of adaptive vs. non-adaptive treatment to identify cost-benefit outcomes from the perspective of smokers, healthcare systems, insurance companies, and employers. Cost assessments of adaptive treatment will include: 1) Descriptive statistics to compare overall cost of medications for adaptive vs. non-adaptive treatment. 2) ANOVA modeling to analyze cost of medications per abstinent smoker comparing adaptive vs. non-adaptive treatment. 3) ANOVA modeling to analyze the cost of prescribed medications as related to medication non-adherence and attrition. 4) Mediation analysis on how randomization status affects medication adherence and how that relationship is mediated by income.

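### Appendix 18 adds the four PSS-4 items without reversing the two positively worded ones, which severely degrades the stress score; neighbouring income, cost, responder and mediator rules need rewording

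*Protocol*

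**What the plan says.** **Stress score.** Appendix 18 prints four items with one response code, 0 = never to 4 = very often. Item 1 asks "how often have you felt that you were unable to control the important things in your life", and item 4 asks about difficulties piling up. Item 2 asks "how often have you felt confident about your ability to handle your personal problems" and item 3 "how often have you felt that things were going your way". The scoring rule is "Calculate: Add scores of above responses", with bands 0–5 low, 6–11 moderate and 12–16 high stress. The protocol states no reversal anywhere. Section 10.7.5 makes the PSS-4 the trial's stress measure. Sections 3.1, 3.6 and 13.5.1 use stress as a predictor, moderator and candidate mediator.

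**Neighbouring rules.**
- Section 13.5.1, Economic Analysis, plans "Mediation analysis on how randomization status affects medication adherence and how that relationship is mediated by income" and "ANOVA modeling to analyze cost of medications per abstinent smoker comparing adaptive vs. non-adaptive treatment".
- Exploratory hypothesis 9 (Section 3.1) covers responder status in both the adaptive and standard arms and concludes: "This finding will show that poor response to pharmacotherapy may be related to high levels of anxiety, depression, or stress".
- Exploratory objective 7 (Section 3.1) says that if a measure changes significantly from baseline to a post-quit time point, "it will be assessed as possible mediator of abstinence outcomes". Section 13.5.1 uses a different screen: whether assignment is associated with change in the construct.

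**The concern.** Frequent agreement with items 1 and 4 means more stress; frequent agreement with items 2 and 3 means less. Adding all four in the same direction sets the two pairs against each other, yet the total is read as though higher always meant more stress. A null result for stress as predictor, moderator or mediator could then reflect the scoring and not the participants. The protocol fixes both the algorithm and the cut-offs, so this is not a detail left open for an analysis plan.

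The neighbouring rules have their own faults. A variable measured before randomisation cannot carry the effect of randomisation. A ratio with the number of abstainers as denominator is not a participant-level outcome. Non-response on placebo is not poor response to a drug. A candidate mediator measured at the same visit as the outcome leaves the direction of effect open.

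**Working it through.** **1. The two totals.** Write N = item 1 + item 4 and P = item 2 + item 3, each 0 to 8.
- As printed: S = N + P.
- With items 2 and 3 reversed: R = item 1 + (4 − item 2) + (4 − item 3) + item 4 = N + 8 − P.

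Both run from 0 to 16, so the printed range and bands are reproduced and the range itself gives no warning.

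**2. Example patterns (items 1, 2, 3, 4).**

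| Pattern | Printed total | Reversed total |
|---|---|---|
| 4,0,0,4 (most stressed) | 8, moderate | 16, high |
| 3,1,1,3 | 8, moderate | 12, high |
| 1,3,3,1 | 8, moderate | 4, low |
| 0,4,4,0 (least stressed) | 8, moderate | 0, low |
| 4,4,4,4 | 16, high | 8, moderate |

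For fully consistent answers (item 2 = 4 − item 1, item 3 = 4 − item 4), P = 8 − N, so S = 8 whatever N is, while R = 2N. All 25 such patterns score 8 as printed and span 0 to 16 after reversal.

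**3. All 5 × 5 × 5 × 5 = 625 patterns.**
- High after reversal (R ≥ 12): 70. As printed, 56 are moderate, 9 low and 5 high.
- The 5 can be checked by hand. R ≥ 12 needs N − P ≥ 4, and S ≥ 12 needs N + P ≥ 12. With N at most 8, only N = 8, P = 4 satisfies both: 1 way × 5 ways = 5, each with R = 12. A respondent with R = 16 has N = 8 and P = 0, so S = 8 and can never be classed high.
- Low after reversal (R ≤ 5): 122. As printed, 90 are moderate, 23 low and 9 high.
- Over the grid, Cov(S, R) = Var(N) − Var(P) = 0, so the correlation is 0.00. The bands agree for 50.4% of patterns. The grid weights every pattern equally and is not a model of real respondents.

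**4. Correlation with latent stress (assumed models).** One factor, 200,000 simulated respondents, symmetric item cut-points at −1.2, −0.4, 0.4 and 1.2, and loadings of 0.5 to 0.8 on items 1 and 4. The protocol gives no item data, so all of this is assumption.

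| Loading of items 2 and 3 relative to 1 and 4 | Printed total | Reversed total |
|---|---|---|
| 100% | −0.002 to 0.002 | 0.737 to 0.920 |
| 80% | 0.108 to 0.210 | 0.692 to 0.885 |
| 60% | 0.205 to 0.368 | 0.639 to 0.844 |

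A separate run with skewed items gave 0.12 to 0.20 for the printed total with equal loadings, and up to about 0.45 with skewed items and unequal loadings together. No reversed-total figures are available for that run.

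**5. Income.** Section 10.1 lists the financial questionnaire, which holds the income item (Appendix 3), among the screening baseline measures. Randomisation happens at the later enrolment visit. Assignment therefore cannot change the recorded income.

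**6. Cost per abstinent smoker.** This is an arm's total medication cost divided by its number of abstainers: one value per arm, and none for a non-abstinent participant. If ANOVA were run on abstainers only, the plan's own rates imply 0.397 × 150 ≈ 60 adaptive and 0.234 × 150 ≈ 35 standard participants, selected on the outcome.

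**7. Hypothesis 9.** Section 10.2 judges response 2 weeks before the target quit day (TQD). In the standard arms, active varenicline starts 1 week before the TQD and active patch on the TQD. Every standard-arm participant is therefore on placebo at that visit.

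**8. Mediator timing.** The outcome window at week 12 opens about day 84 − 30 = 54 after the TQD. Week-2 scores (day 14) precede it. Week-12 scores come from the same visit as the outcome, and the PSS-4 asks about the last month, roughly the same window.

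**The case against.** **Is the score pure noise?** A reader might infer that the printed total cannot measure stress at all. The documents do not support that. A correlation of zero needs equal loadings and symmetric items; otherwise a weak signal of roughly 0.1 to 0.45 remains. This part of the objection stands. The fault also concerns stress only: Appendices 16 and 17 sum the depression and anxiety items without this problem.

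**Does any measure that changes become a mediator?** A reader might take objective 7 that way. It says only that such a measure will be assessed as a possible mediator, and Section 13.5.1 already screens on association with assignment. The constructs listed there are measured after randomisation and can be mediators. What remains is that the two screens differ and that week-12 scores are eligible. The week-6 call is no substitute source for the standardised scales: Appendix 19 contains no PSS-4, PHQ-2 or GAD-2.

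**Should hypothesis 9 use the adaptive arm alone?** That is tempting, but it would discard the placebo comparator. Without the standard arm, an effect of stress on drug response cannot be separated from a general tendency not to cut down. The hypothesis is also hedged. Only its interpretive sentence needs work.

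**Is the cost line just loose wording?** Partly. The text does not say that the ANOVA is restricted to abstainers, and estimation detail could sit in an analysis plan that was not available. But the named quantity has no participant-level value for non-abstainers, so the named method does not fit it.

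**Does it matter?** The PSS-4 is not an eligibility criterion, and everything affected is exploratory or economic. That stands and limits the weight of the point.

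**Conclusion.** The PSS-4 rule is wrong as written. This follows from the item wording, the common response code and the printed bands, with no outside scoring manual. The best exact measures of its size are that opposite extremes both score 8, that a maximally stressed respondent can never be classed high, and that 5 of 70 high patterns keep that label. The correlations describe severe degradation but rest on assumed one-factor models.

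The income-mediator wording is also wrong on the protocol's own timing of measurement, and ANOVA is the wrong tool for a cost-per-abstainer ratio. Hypothesis 9 and the mediator rules need narrower corrections.

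A reader might infer that the trial's main result is at risk. It is not: the primary endpoint, N = 300 and the stated 87% power do not depend on any of these rules. The change should be made because it is cheap and because stress results would otherwise be hard to interpret.

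**What to change.** - **Appendix 18:** score items 2 and 3 as 4 minus the response before summing and banding. Rescore data already collected from the item responses.
- **Section 13.5.1, Economic Analysis:** replace income as mediator with income as a baseline moderator (arm × income) or covariate. Compare cost per abstinent smoker as an arm-level, incremental ratio with a bootstrap interval in place of ANOVA.
- **Section 3.1, hypothesis 9:** keep both arms. Reword the conclusion so that a drug-response claim rests on the baseline score × arm interaction, not on non-response pooled over both arms.
- **Sections 3.1 and 6, with 13.5.1:** apply the Section 13.5.1 screen (change associated with assignment) throughout. For mediation of 12-week abstinence, use the week-2 visit scores.

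The cost is scoring code and plan wording. No new data are needed, provided item-level PSS-4 responses have been kept.
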